### Data collection

#### Baseline characteristics

Baseline characteristics from patients, clinicians, and hospitals will be collected in the following manner:

1. Patients: From PALGA, data including age, gender, and some medical information will be collected. Medical information includes diagnoses of cancer (diagnosed since 1971), cancer type, and age at diagnosis, as well as the result of MSI testing. The following data will be collected by a self-administered questionnaire: ethnicity, current marital status, educational level, previous medical or health training, and family history of cancer (type of cancer and age at diagnosis). Family history is collected for first-degree relatives (*i.e*., parents, siblings, and children).

2. Clinicians: All participating clinicians will be asked to provide baseline data (*e.g*., specialization, number of years of experience) in a questionnaire

3. Hospitals: From the hospitals' websites, characteristics such as size, teaching status, and presence of an outpatient department for genetic counselling will be obtained.

#### Effect evaluation

Before introducing the implementation strategies, a baseline assessment of risk calculation, interpretation, and communication will be performed. Both the baseline assessment and the evaluation of the implementation strategies will be performed retrospectively in the same manner. Baseline characteristics will be collected in the manner described above. The measuring instruments will be developed by identifying all relevant variables and translating these into questionnaires. When possible, existing validated questionnaires will be used.

The family history as reported by the patient in the questionnaire will be used to calculate a formal familial CRC risk and determine the indicated follow-up policy. This will be compared to the family history taken by the clinician, along with the risk calculation and interpretation performed by the clinician. These data will be extracted from the patients' medical records. The medical records will also be used to determine the number of patients with whom the familial CRC risk and corresponding follow-up policy has been communicated. To determine the number of referred patients who actually visit a familial cancer clinic, these clinics will be asked to report whether these patients have visited. The uptake of surveillance by colonoscopy by first-degree relatives will be determined by asking the patients whether their relatives are actually screened. Medical records and results from the decision aids on the website will be used to determine whether patients at an increased risk who were not referred for surveillance or genetic counselling were not referred because they had chosen not to be referred or because it was not discussed.

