## Background

The lifetime risk of developing colorectal cancer (CRC) in Western society is 5 to 6%[1,2]. Familial and hereditary cancers account for approximately 15 to 20% of all CRCs [3-5]. In these families, healthy relatives of CRC patients may have an increased risk of developing CRC themselves. This so-called familial CRC risk can be divided into three groups, based on cumulative lifetime risks of developing CRC:

1. Average: familial CRC risk below 10%.

2. Moderate: familial CRC risk of 10-15%.

3. High: familial CRC risk above 15%.

For each group, a different follow-up policy applies. For individuals with an average familial CRC risk, neither surveillance nor genetic counselling is indicated. For individuals with a moderate familial CRC risk, surveillance by regular colonoscopy is indicated. For individuals with a high familial CRC risk, referral for genetic counselling is recommended. Identification of individuals with an increased familial CRC risk is crucial because surveillance significantly reduces CRC-related morbidity and mortality, by 43 to 80% and 65 to 81%, respectively[6,7]. Both underuse and overuse of surveillance and genetic counselling have a significant impact on patients and their relatives, and may lead to unnecessary costs.

Familial CRC risk is assessed by family history and, in a subset of patients, microsatellite instability (MSI) analysis performed by pathologists. Unfortunately, both procedures are difficult. Previous research has shown that patient family history often is missing or incomplete, and information provided by patients is not always accurate[4,8-11]. Furthermore, interpretation of the family history (determining the indicated follow-up policy) is not always correct[12]. Pathologists' selection of patients for MSI is often incomplete, while clinicians regularly interpret the results incorrectly [Overbeek LI, Hermens RP, van Krieken JH, Adang E, Casparie M, Akkermans R, Nagengast FM, Ligtenberg MJ, Hoogerbrugge N. A tailored implementation strategy increases involvement of pathologists in the recognition of patients at risk for Lynch syndrome: cluster randomised controlled trial, submitted] Consequently, only 12 to 30% of CRC patients with a high familial CRC risk are referred for genetic counselling[4,10,13-15]. Other studies have shown that many CRC patients referred to a familial cancer clinic belong to an average or moderate risk population for whom genetic counselling is not indicated[16,17].

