### Outcome measures

#### Effect evaluation

1. The percentage of CRC patients for whom a correct familial CRC risk is calculated by clinicians.

2. The percentage of CRC patients for whom a calculated familial CRC risk is correctly interpreted by clinicians.

3. The percentage of CRC patients with whom a calculated familial CRC risk and/or follow-up policy is communicated by clinicians.

4. Patients' uptake of the indicated follow-up policy.

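### The reference risk used to score clinicians is built from patient-reported family history with no other input named, although the protocol treats MSI as part of risk assessment and already collects it

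*Protocol article*

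**What the plan says.** Three places in the protocol article bear on this.

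- **Background**, on what risk assessment consists of: "Familial CRC risk is assessed by family history and, in a subset of patients, microsatellite instability (MSI) analysis performed by pathologists". The same paragraph adds that clinicians often misread MSI results.
- **Data collection, Baseline characteristics**, on what is held. PALGA supplies the patient's cancer diagnoses, cancer types and ages at diagnosis, "as well as the result of MSI testing". The self-administered questionnaire supplies the family history, limited in extent: "Family history is collected for first-degree relatives".
- **Data collection, Effect evaluation**, on the reference: "The family history as reported by the patient in the questionnaire will be used to calculate a formal familial CRC risk", and from it the indicated follow-up policy. The next sentence sets the comparison: "This will be compared to the family history taken by the clinician, along with the risk calculation and interpretation performed by the clinician".

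The limitations in the Discussion consider how accurate reported family history is. They do not mention MSI.

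**The concern.** A reference standard should contain at least the information that the assessment being judged is meant to use. Here the clinician is expected to work from family history and, in some patients, an MSI result, while the reference is described as resting on family history. In a patient whose category turns on MSI, the two can disagree because the reference is incomplete, and the disagreement is charged to the clinician.

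The first effect outcome is "The percentage of CRC patients for whom a correct familial CRC risk is calculated by clinicians", and what counts as correct is decided by this reference. So is the policy that counts as indicated, and hence who belongs to the moderate-risk and high-risk groups on which the sample size is based. The protocol also gives clinicians' misreading of MSI results as part of its motivation, and a reference without MSI cannot detect that failing.

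**Working it through.** **1. The inputs side by side**

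| Item | Background: part of risk assessment | Baseline characteristics: collected | Effect evaluation: named as input to the reference |
|---|---|---|---|
| Family history | yes | yes, questionnaire | yes |
| MSI result | yes, in a subset | yes, PALGA | no |
| Patient's own cancers and ages at diagnosis | not named there | yes, PALGA | no |

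On the last row, the legend to Figure 1 defines familial risk as that of the CRC patient's first-degree relatives, and the Abstract names a relative with early-onset CRC as a risk criterion. The patient's own cancer and age at diagnosis are therefore relevant too.

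**2. One patient traced through the scoring rules**

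Suppose a patient's family history alone gives average risk, the guideline would place the patient at high risk once the MSI result is counted, and the patient wants referral. (This is hypothetical; the documents do not set out the guideline's MSI rule.)

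| Clinician | Scored against family history only | Scored against family history plus MSI |
|---|---|---|
| Uses MSI, rates high, refers for genetic counselling | calculation wrong, referral wrong | calculation right, referral right |
| Ignores MSI, rates average, does not refer | calculation right, referral right | calculation wrong, referral wrong |

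The referral scores follow from Data analysis, Effect evaluation, where an average-risk patient counts as correctly referred only if not referred. Every score reverses with the choice of reference.

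**3. Which measures depend on the reference**

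- Outcome 1, correct calculation: yes.
- Outcome 2, correct interpretation: probably. The Background equates interpretation with determining the indicated policy, but the outcome is worded for a risk that has been calculated and could be judged against the clinician's own figure.
- Outcome 3, communication: no. It records from the medical record whether risk or policy was communicated.
- Outcome 4, uptake of the indicated policy: yes.
- Correct-referral categories and cost per correctly referred patient: yes.

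**4. The plan's own figures**

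The sample size is not in dispute. The base rate is not stated. Assuming 30% versus 50% (or 50% versus 70%), two-sided alpha 0.05 and power 0.80, the usual two-proportion formula gives 93 per arm, 2 × 93 = 186. The design effect is 1 + (5 − 1) × 0.15 = 1.6, and 186 × 1.6 = 297.6, against the stated 60 × 5 = 300.

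**5. What misclassification could cost, by assumption only**

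Take a true difference of 40% versus 60% and an effective sample of 300 / 1.6 = 187.5 patients; power is 0.79. Let a fraction m of scored patients have a wrong reference category, equally in both arms. If their scores carry no arm difference, the observed difference is 20 × (1 − m) points. If their scores are reversed, it is 20 × (1 − 2m) points.

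| m (assumed) | No arm difference: points, power | Reversed: points, power |
|---|---|---|
| 5% | 19, 0.74 | 18, 0.70 |
| 10% | 18, 0.70 | 16, 0.59 |
| 20% | 16, 0.59 | 12, 0.38 |

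The documents give no value for m, so the table shows sensitivity and is not an estimate.

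**The case against.** The strongest reply is that the sentence is shorthand. It contains no word of exclusion. It may name the questionnaire only to contrast the patient's account with the clinician's, as the next sentence does. It cannot be a full list, since it omits even the patient's own CRC. The same section refers back to the baseline data, which include MSI, and a condensed article may leave the scoring algorithm to the full protocol.

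Part of this stands: that family history is the sole input is an inference. But the article does state what the reference is calculated from, and nothing in it, including the limitations, brings MSI in. Someone who followed the text would build an incomplete reference.

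Three stronger readings are tempting and not supported:

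- **All four effect outcomes are affected.** Outcome 3 needs no reference risk.
- **The bias has a known direction.** A reader might infer that the omission penalises the intensive arm and hides a benefit. Both arms receive the guideline, and the described risk tool takes medical information about patients and relatives without mentioning MSI. Nothing shows that the intervention changes MSI-based referral in particular.
- **The questionnaire is contaminated by the website.** The evaluation is described this way: "Both the baseline assessment and the evaluation of the implementation strategies will be performed retrospectively in the same manner". Logins are issued at inclusion, so a reader might infer that intervention patients report their history after using the tool. The documents do not date the questionnaire relative to login. Moving it to consent could itself prompt control patients.

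Nor can the share affected be derived from the 15 to 20% in the Background. That is the share of CRCs that are familial or hereditary, not the share classified as at risk by family history.

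**Conclusion.** The concern holds as an inconsistency in a stated rule. The Background makes MSI part of risk assessment in a subset, the baseline section collects it, and the effect evaluation names only family history when it defines the reference. As written, outcomes 1 and 4, probably outcome 2, the correct-referral categories and the cost denominator would misclassify patients whose category depends on MSI.

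Its size is unknown. It is confined to patients whose category changes once MSI is counted, and the documents do not say how many there are. No direction of bias between arms is established. The conclusion rests on reading the sentence as a description of the inputs actually used; if the full protocol adds MSI, the article's wording needs correcting and the scoring does not.

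**What to change.** Reconcile the Background, Baseline characteristics and Effect evaluation sections by stating whether and how MSI enters the reference. Specifically:

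- Define the formal risk and indicated policy from questionnaire family history plus the PALGA data already held: MSI result, the patient's own cancers and ages at diagnosis.
- Apply one algorithm identically in both arms, by assessors who have not seen the clinician's assessment.
- Report the family-history-only version as a sensitivity analysis, with the number of patients in each arm whose category differs between the two. That count supplies the size that is now missing.

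This costs about one sentence in the outcome definition and one additional analysis. No new data are needed. It should be settled before scoring starts, because changing the reference afterwards would invite doubt about the result.

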## Methods

### Study design and setting

A clustered randomized controlled trial including an effect, process, and cost evaluation will be conducted in eighteen community hospitals. All patients with CRC diagnosed under the age of 70 years and their clinicians will be invited to participate. To prevent contamination bias, randomization will take place at hospital level. Stratification will take place according to hospital size (<500, 500 to 700, and >700 beds), and be performed by means of a computerized randomization system. This study was approved by the Committee on Research Involving Human Subjects of the region Arnhem-Nijmegen.

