#### Website

The website consists of the following items:

1. A summary of evidence-based and relevant information about familial CRC risk (lifetime risk of developing CRC). Natural frequencies with the same denominator and visual displays will be used. Absolute risks will be presented, as well as in comparison to the population risk. The outcomes are offered in both positive and negative frames (*e.g*., the risk of developing CRC as well as the chance of not developing CRC). The focus is on familial CRC risk and the different follow-up policies. The information is presented in two different formats, one for patients and one for clinicians.

2. A risk assessment tool to calculate patients' familial CRC risk. Patients fill in medical information about themselves and their relatives with regard to CRC and other cancers. Clinicians can use the tool as well. The calculated familial CRC risk is given in the same format as the rest of the website. Advice for follow-up is offered based on this risk, as well as a reminder to use the corresponding decision aid, if applicable.

3. Decision aids, aimed at facilitating decisions involving the uptake of the indicated follow-up policy (one for surveillance and one for genetic counselling). Tools supporting patients in making informed choices about their healthcare, such as decision aids, have been shown to improve knowledge, clarify preferences, and reduce uncertainty around decision making, with high levels of acceptability among consumers[20,21]. The decision aids used in this trial provide balanced information on different options, *i.e*., to be referred for surveillance/genetic counselling or not. The following items are addressed: background information, benefits and harms, and the potential impact on the patient and their relatives. Worksheets are provided for patients to list and rate the importance of the benefits and harms for themselves.

The website is available exclusively to patients and clinicians in the intervention group. A login name and password will be provided upon inclusion. Patients can use the website independently before or after regular follow-up visits, and are encouraged to discuss the results with their clinician. They are instructed to keep the decision aid within their family, and not share it for reasons of research integrity. To minimize contamination bias, after the trial all patients in the control group will be asked if they were exposed to the website.

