### Data analysis

#### Effect evaluation

To analyze the effectiveness of both implementation strategies, descriptive statistics and multilevel analysis will be used. Patient, clinician, and hospital characteristics will be included in the multilevel analysis, allowing for correction of the effectiveness for probable differences in case mix between the different hospitals. The statistical analyses will be performed using SPSS version 16.0 for Windows.

The percentage of correctly referred patients is defined as follows:

1. The percentage of patients at an average familial CRC risk who are not referred for surveillance or genetic counselling.

2. The percentage of patients at a moderate familial CRC risk who want to be referred and are referred for surveillance.

3. The percentage of patients at a moderate familial CRC risk who do not want to be referred and are not referred for surveillance.

4. The percentage of patients at a high familial CRC risk who want to be referred and are referred for genetic counselling.

5. The percentage of patients at a high familial CRC risk who do not want to be referred and are not referred for genetic counselling but are referred for surveillance if they opt for it.

6. The percentage of patients at a high familial CRC risk who do not want to be referred and are not referred for genetic counselling or surveillance.

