### Strengths and weaknesses

To our knowledge, this is the first study of an implementation strategy designed to improve the recognition of patients' familial CRC risk by addressing both patients and their clinicians (surgeons and gastroenterologists). If the intensive implementation strategy is successful, the elements (the website and the risk communication tool) can be released for general use by patients and clinicians. They may also serve as an example for other hereditary and non-hereditary diseases. Our study will add knowledge to the effectiveness of patient decision aids and the best way of supplying patients and clinicians with information on disease risks.

Some limitations need to be addressed. Family history as reported by the clinician will be compared to the family history reported by the patient in a self-administered questionnaire. Previous research has shown that the accuracy of family history of CRC in first-degree relatives reported by patients is approximately 90%[22]. The optimal way of ensuring that the family history reported by the patient is accurate is by reviewing medical records of the affected relatives. Since written permission from relatives is needed to do so, this is not feasible and will therefore not be done in this study.

In our evaluation, only patients will be included; their relatives are not. Patients will be asked whether their relatives are screened, but the relatives will not be contacted to assess whether they actually received the results from the risk assessment and the matching advice.

Measurements may be contaminated in case others are provided with the login code for the website.

Collecting data from medical records does not monitor everything that is discussed between the clinician and the patient. This may lead to underestimation of the risk interpretation and communication. Videotaping the consultations would shed light on the content and quality of the risk communication, but would also influence the intervention by reminding the clinician of the intervention. In this study, regular clinical practice will be left undisturbed as much as possible.

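### Refusals count as correct referral, but they are judged partly from decision-aid results that only the intervention arm can have

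*Protocol article*

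**What the plan says.** Data collection, Effect evaluation, names these sources.

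- **Clinician's family history, risk calculation and interpretation:** "These data will be extracted from the patients' medical records". They are compared with a formal risk and policy worked out from the patient's questionnaire.
- **Communication:** "The medical records will also be used to determine the number of patients with whom the familial CRC risk" and the matching policy were communicated.
- **Attendance at a familial cancer clinic:** "these clinics will be asked to report whether these patients have visited". Relatives' colonoscopies are reported by the patients.
- **Reason for non-referral:** "Medical records and results from the decision aids on the website will be used to determine whether patients at an increased risk". The judgement is whether a patient without referral had chosen this, or whether the subject had not come up.

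Two other sections bear on the last item. Interventions, Website, states: "The website is available exclusively to patients and clinicians in the intervention group". Data analysis, Effect evaluation, lists six groups that make up correct referral. Three of them rest on the patient not wanting a referral, for example: "The percentage of patients at a moderate familial CRC risk who do not want to be referred and are not referred for surveillance". The cost evaluation then relates costs to the number of correctly referred patients.

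**The concern.** Whether a non-referred patient declined or was never asked decides whether that patient counts as a success or a failure. In the control arm a refusal is found only if the notes mention it. In the intervention arm it can also be found on the website. Two problems follow from the procedure as written.

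1. **Unequal detection.** The same share of true refusals yields more recorded refusals, and so more correct referrals, in the intervention arm.
2. **Arm revealed at the point of judgement.** Opening a decision-aid result beside the record tells the scorer the arm while an incomplete note is being classified.

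Both can raise the intervention arm's percentage of correct referral and lower its cost per correctly referred patient. The planned multilevel model corrects for differences in case mix. It cannot remove an error that runs along the arm itself.

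**Working it through.** **The plan's own figure.** The article gives no figure for this classification. Its sample size reproduces and is not in dispute. A 20-point difference such as 30% v 50% needs 93 per arm, or 186. The design effect is 1 + (5 − 1) × 0.15 = 1.6, and 186 × 1.6 = 297.6, rounded up to 300. That target concerns surveillance uptake and referral for genetic counselling, so the bias below is not expressed as a fraction of it.

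**The chain in the text.**

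1. The reason for non-referral uses records plus decision-aid results (Data collection).
2. Decision-aid results exist in one arm only (Website).
3. Refusal without referral counts as correct (Data analysis).
4. The same count enters the cost evaluation.

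Each step is stated, and none depends on who does the extraction.

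**Illustration of unequal detection, with no true difference between arms.** All four inputs are assumptions; none is in the article.

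- u = share of increased-risk patients not referred: 30% to 70%
- d = share of those who truly declined: 20% to 40%
- s = share of refusals visible in the notes: 50% to 80%
- a = share of the remaining refusals visible in a decision aid: 30% to 60%

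Referred patients are taken as correct. A website result is assumed never to overturn a refusal in the notes.

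Control: (1 − u) + u·d·s

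Intervention: (1 − u) + u·d·[1 − (1 − s)(1 − a)]

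False gain: u·d·(1 − s)·a

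| Case | u, d, s, a | Control | Intervention | False gain |
|---|---|---|---|---|
| Low | 0.30, 0.20, 0.80, 0.30 | 74.8% | 75.2% | 0.30 × 0.20 × 0.20 × 0.30 = 0.4 points |
| Middle | 0.50, 0.40, 0.50, 0.60 | 60% | 66% | 0.50 × 0.40 × 0.50 × 0.60 = 6 points |
| High | 0.70, 0.40, 0.50, 0.60 | 44% | 52.4% | 0.70 × 0.40 × 0.50 × 0.60 = 8.4 points |

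**Cost.** With the same spending per patient, cost per correctly referred patient scales with control ÷ intervention. In the middle case 60/66 = 0.91, so it looks about 9% lower with no real change. In the high case 44/52.4 = 0.84, about 16% lower.

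These figures apply to increased-risk patients. If average-risk patients are pooled into the same percentage, the gain shrinks in proportion to the share at increased risk. The second problem, knowledge of arm when a note is read, is not quantified because the article offers nothing to base it on.

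**The case against.** The strongest reply is that this is a condensed article. It does not say who extracts the records, whether they know the allocation or whether a fixed form is used, and such details may stand in the full protocol. That is right, and it limits the point.

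A reader might infer that staff know each hospital's arm and tilt every record-based outcome. The reasoning would be that "To prevent contamination bias, randomization will take place at hospital level" and that, by the article's own admission, "Collecting data from medical records does not monitor everything that is discussed between the clinician and the patient". The document does not support this, for four reasons.

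- A hospital's name reveals the arm only to someone who holds the allocation.
- Decision-aid results are specified for the reason for non-referral only, not for scoring calculation, interpretation or communication.
- Correctness is judged against a formal risk from a separate source, the questionnaire, which limits discretion.
- Clinic visits and relatives' screening do not come from hospital notes.

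One could assume that 20% of notes are ambiguous and credited 25 points more often in one arm, giving 0.20 × 0.25 = 5 points. Neither input is in the article, so that figure is no evidence of a flaw.

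A second reply is that baseline and evaluation are assessed in the same way. This does not help here. The baseline precedes the strategies, so no decision-aid result exists then in either arm, and the extra source enters only at evaluation.

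A third reply is that refusals found on the website are real. They may be, but equally real refusals in the control arm go unrecorded, and the comparison is between arms.

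**Conclusion.** The point holds for the reason for non-referral, the percentage correctly referred, and the cost per correctly referred patient. There the written procedure shows the scorer the arm and gives the intervention arm an extra way to be credited. This is a stated choice, not a gap that a fuller protocol would simply fill.

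It is not shown that the three outcomes on calculation, interpretation and communication are scored with knowledge of arm. The likely direction favours the intervention. The size cannot be derived from the article. The range of 0.4 to 8.4 points rests wholly on the four assumed rates and covers only unequal detection.

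**What to change.** Put the work in Data collection, Effect evaluation, into a fixed order.

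1. Compute the formal risk and indicated policy from the questionnaire, and lock them before the record is opened.
2. Code referred, declined or not discussed from the medical record alone, by the same written rules in both arms. Lock this coding for the main comparison and the cost evaluation.
3. Open decision-aid results only afterwards. Use them in a sensitivity or process analysis, without changing the locked codes.
4. Where the existing team allows, give the coding to a member who is not told the hospital's allocation.

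The order of steps 2 and 3 matters most. Masking alone would leave the one-arm source in place.

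The cost is protocol wording, some reordering and a little more handling per record. Steps 1 to 3 need no new data or staff. The drawback is that refusals recorded only on the website are missed in the main analysis, so correct referral may be understated in the intervention arm, as it already is in the control arm wherever the notes are silent. If that loss is unacceptable, the patient's wish could be asked in the same way in both arms, at the price of an added item.

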#### Power calculation

To detect a difference of 20% between the intervention group and the control group in uptake of surveillance by colonoscopy in patients at moderate familial CRC risk, and referral for genetic counselling in patients at a high familial CRC risk, at least 186 patients are required (alpha = 0.05, a two-sided testing and power = 0.80). However, considering an intracluster-correlation coefficient of 0.15 and an average of five patients per clinician, at least sixty clinicians and 300 patients are needed. For eighteen hospitals this means three to four clinicians and 15 to 20 patients per hospital.

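### Familial cancer clinics report only on referred patients, so counselling reached without a known referral is unseen, and any such loss could be larger in the intervention arm

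*Protocol article*

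**What the plan says.** Effect outcome 4 in the protocol article (Outcome measures) is "Patients' uptake of the indicated follow-up policy". The same idea appears in the primary objective and the hypothesis. According to the Background, the indicated policy at high familial risk is genetic counselling.

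For attendance at counselling, the Effect evaluation section under Data collection determines the "number of referred patients who actually visit a familial cancer clinic, these clinics will be asked to report whether these patients have visited". For at-risk patients who were not referred, that section uses medical records and decision-aid results, but only to learn why: either the patient declined, or the matter was never raised. Patients are asked about their relatives' colonoscopy. No question about their own counselling is described.

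The Website section gives intervention-arm patients, and no others, a tool that calculates their risk. It adds: "Advice for follow-up is offered based on this risk, as well as a reminder to use the corresponding decision aid, if applicable". Patients may use it on their own between visits and are encouraged to take the results to their clinician. Controls get guideline dissemination to clinicians and nothing aimed at patients.

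**The concern.** Outcome 4 is about what patients do, but attendance is looked up only in those for whom the clinician's step, referral, is already known to have happened. Referral occurs after randomisation, and the strategy is meant to change it. Making the lookup depend on it means that true non-attendance cannot be told from attendance nobody asked about.

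The intensive strategy works through patients as well as clinicians. If its patient-directed part led some patients to counselling without a referral known to the study, those visits would be lost, and the tools that could prompt them exist in one arm only. The uptake comparison would then lean towards no difference. The process evaluation, which asks which elements were associated with success, would understate the patient-directed ones.

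The opposite error is hidden too. The Data analysis section counts average-risk patients as correct when they are not referred, so counselling they reached without referral would go unnoticed. The Background names overuse as a concern.

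**Working it through.** **1. Who is looked up, and what is recorded**

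| Patient at high familial risk | Clinic asked? | Other source for own attendance | Likely entry for outcome 4 |
|---|---|---|---|
| Referred, attends | yes | none needed | uptake |
| Referred, does not attend | yes | none needed | no uptake |
| Not known to be referred, does not attend | no | none named | no uptake (declined or not raised) |
| Not known to be referred, attends | no | none named | probably no uptake (declined or not raised) |

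The last two rows cannot be separated with the data described. The entry in the last row follows from the data flow; the article does not write it as a rule.

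**2. The protocol's own figures**

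Inputs from Power calculation: "alpha = 0.05, a two-sided testing and power = 0.80"; "To detect a difference of 20% between the intervention group and the control group"; "at least 186 patients are required"; "considering an intracluster-correlation coefficient of 0.15 and an average of five patients per clinician"; "at least sixty clinicians and 300 patients are needed". No base rate is given.

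Per arm, n = [1.96·√(2p̄(1−p̄)) + 0.8416·√(p₁(1−p₁)+p₂(1−p₂))]² / (p₂−p₁)².

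With 30% and 50%, p̄ = 0.40: (1.96·√0.48 + 0.8416·√0.46)² / 0.04 ≈ 93 per arm, or 186 in total. By symmetry, 50% and 70% also give 186. The pairs 40%/60% and 20%/40% give 194 and 164, which do not match.

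Design effect: 1 + (5−1)·0.15 = 1.6. Then 186·1.6 = 297.6, and 297.6/5 = 59.5, so 60 clinicians and 300 patients.

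Both figures reproduce, and the sample size is not in dispute. Its use here is to supply two plausible base-rate pairs.

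**3. Illustration among high-risk patients only**

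Assumptions: true attendance follows one of the two pairs above, and a share of it in each arm is missed because no referral is known. The documents give no such share, so the range starts at zero. Observed difference = p₂(1−missed in intervention) − p₁(1−missed in control).

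| Missed, intervention / control | 30% vs 50% | 50% vs 70% |
|---|---|---|
| 0% / 0% | 20 points | 20 points |
| 10% / 10% | 45 − 27 = 18 | 63 − 45 = 18 |
| 5% / 0% | 47.5 − 30 = 17.5 | 66.5 − 50 = 16.5 |
| 10% / 2% | 45 − 29.4 = 15.6 | 63 − 49 = 14 |

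Equal loss shrinks the difference only in proportion. Unequal loss shrinks it further.

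**4. What the table does not show**

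The 20 points in Power calculation refer to colonoscopy uptake at moderate risk together with referral for counselling at high risk. Clinic attendance is not in that endpoint, and the split between moderate and high risk is not given. The table therefore cannot be turned into a loss of power for the planned 300 patients.

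**The case against.** The best defence is that the article describes no way to reach counselling except by referral. The website directs patients to discuss results with their clinician, and the decision aids set out a choice between being referred and not. A patient prompted by the website is thus steered into the pathway that is measured. This stands, and it is why the size of the loss is unknown and may be zero.

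Direction is also uncertain in part. Referrals that the study does not learn of could occur in either arm, and trained clinicians might document better. Only attendance prompted by the patient-directed tools gives a reason to expect more loss in the intervention arm. Such loss would bias the comparison towards no difference.

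Three stronger readings are tempting but unsupported:

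- A reader might infer that the website does send patients around their clinician. No passage says so.
- A reader might cite the limitation in the Discussion about medical records as an admission that referrals go unrecorded. It concerns what is said in consultations and the underestimation of risk interpretation and communication. It does not mention referral, and the article does not state outright that referral is read from the hospital record.
- A reader might assume losses of 10 and 2 percentage points, giving 40 − 28 = 12, and set this against the 20 points in Power calculation. Those losses have no source, and the high-risk part of that endpoint is referral, not attendance.

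It may also be said that a condensed article leaves such details to the full protocol. That would cover an omission. Here the article states whom the clinics are asked about, and the restriction lies in that statement.

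**Conclusion.** The point holds as a risk of unequal under-ascertainment in effect outcome 4. The lookup is limited to referred patients, no other source for a patient's own counselling is named, and the patient-directed tools exist in one arm only. If attendance without a known referral occurs, it is missed, and the loss could be greater in the intervention arm.

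The size cannot be derived from the documents. Under the assumed shares, the observed difference among high-risk patients runs from 20 points (nothing missed) to 14 points (10% and 2% missed, base rates 50% and 70%). This rests on three assumptions: the base-rate pairs, the missed shares, and that an unseen visit is entered as no uptake. The powered endpoint is not directly affected. The change is worth making because the gap cannot be repaired or measured from the data as planned, and closing it is cheap.

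**What to change.** In Data collection, Effect evaluation:

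- Ask the familial cancer clinics about all included patients, in both arms and at both assessments, whether or not a referral is known. Make sure that consent covers this lookup.
- Count a visit as uptake for outcome 4 only in patients whose formal familial risk is high, because counselling is the indicated policy for that group alone.
- Use one time window for both arms, starting at inclusion or at introduction of the strategy, with an equivalent window for the baseline assessment. Counting from diagnosis would credit visits made before the website was available.
- Report visits by average- and moderate-risk patients separately, as possible overuse.
- Keep referral by the clinician as an outcome of its own, so that clinician behaviour and patient uptake can be read apart.

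The cost is a longer list sent to clinics that are already being contacted, and one added line in the consent form.
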